#### 4 Primary Outcome – Participant AF knowledge at 90 days

##### 4.1 Primary Outcome Determination

The primary outcome of this study is knowledge of AF medications at 90 day follow up.

This will be defined as the overall score for participants (out of 100%) for participants on the Jessa Atrial Fibrillation Knowledge Questionnaire (JAFKQ).

##### 4.1.1 Primary and key secondary outcome Analysis

The primary outcome will be analysed utilising an analysis of covariance (ANCOVA) comparing scores between intervention and control groups and adjusting for age, gender, educational level and sub-type of AF.

The primary outcome will also be analysed utilising a two tailed t-test comparing the mean score on the JAFKQ between intervention and control participants. Primary and secondary analysis is described in etable 9.

eTable 9: Primary and key secondary outcome analysis

|                                                                    | Control
NC (%)   | Intervention
NT(%) | RR [95% CI]
(Control vs
CPR video)
[unadjusted] | RR [95% CI]
(Control vs
CPR video)
[adjusted] | p-value
[adjusted] |
|--------------------------------------------------------------------|----------------------------------------|------------------------------------------|--------------------------------------------------------------------|------------------------------------------------------------------|-------------------------------|
| Jessa Atrial Fibrillation Knowledge Questionnaire score (%) |                                        |                                          |                                                                    |                                                                  |                               |
| Mean score 2 days
post intervention                             | (n=xx)
Mean (SD)
Median
(IQR) | (n=xx)
Mean (SD)
Median (IQR)      |                                                                    | Mean
Difference
(95% CI)                                   | p-value                       |

| Mean score 90 days post intervention                | (n=xx)
Mean (SD)
Median
(IQR) | (n=xx)
Mean (SD)
Median (IQR) |  | Mean Difference
(95% CI) | p-value |
|-----------------------------------------------------|----------------------------------------|-------------------------------------|--|-----------------------------|---------|
| Satisfaction                                 |                                        |                                     |  |                             |         |
| Highly satisfied*                                   | (n=xx)
Proportion (%)               | (n=xx)
Proportion (%)            |  | RR (95% CI)                 | p-value |
| Motivation to maintain medication adherence  |                                        |                                     |  |                             |         |
| Highly motivated* 2 days post intervention          | (n=xx)
Proportion (%)               | (n=xx)
Proportion (%)            |  | RR (95% CI)                 | p-value |
| Highly motivated* 90 days post intervention         | (n=xx)
Proportion (%)               | (n=xx)
Proportion (%)            |  | RR (95% CI)                 | p-value |
| Medication adherence                         |                                        |                                     |  |                             |         |
| Adherent** to medications 90 days post intervention | (n=xx)
Proportion (%)               | (n=xx)
Proportion (%)            |  | RR (95% CI)                 | p-value |

\*Highly motivated/satisfied = Reported motivation to maintain medication adherence/satisfaction with clinical care  $\geq 6$  on a 7-point likert scale

## 5 Secondary outcome analysis

### 5.1 Satisfaction with clinic experience, motivation to maintain medication adherence and medication adherence – outcome determination

Satisfaction with clinic experience will be determined by a score of  $\geq 6$  on a 7-point Likert scale. The proportion of participants achieving this outcome will be compared between intervention and control groups.

Motivation to maintain medication adherence will be determined by a score of  $\geq 6$  on a 7-point Likert scale. The proportion of participants achieving this outcome will be compared between intervention and control groups.

Medication adherence will be determined by responses to the following questions (previously validated for patients with coronary artery disease and utilised in large scale studies of patients with AF):

- 4) **Specific to your atrial fibrillation medication, in the past month, how often did you take your medications as the doctor prescribed?**
  - a. All of the time (100%)
  - b. Nearly all of the time (90%)
  - c. Most of the time (75%)
  - d. About half the time (50%)
  - e. Less than half the time (<50%)
  - f. No atrial fibrillation medication
- 5) **Specific to your atrial fibrillation medication, in the past month, how often did you forget to take one or more of your prescribed medications?**
  - a. Never
  - b. Once
  - c. 2-3 times
  - d. Once per week
  - e. Several times per week
  - f. Nearly every day
  - g. No atrial fibrillation medication
- 6) **Specific to your atrial fibrillation medication, in the past month, how often did you decide to skip one or more of your prescribed medications**

- a. Never
- b. Once
- c. 2-3 times
- d. Once per week
- e. Several times per week
- f. Nearly every day
- g. No atrial fibrillation medication

Non-adherence will be defined as per previous studies:

- 7. Response to question 1 of “Most of the time (75%) or less OR
- 8. Response to question 2 of “once per week” or more OR
- 9. Response to question 3 of “once per week” or more OR

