## **6. Assessment of outcomes:**

### **Primary Outcome:**

The primary outcome will be the difference in participant percentage score on the JESSA Atrial Fibrillation Knowledge Questionnaire (JAFKQ) in the intervention arm with reinforcement compared to the control at 90 day follow up.

Secondary outcomes assessed at end of clinic (outpatients)/within 2 days (inpatients) will include atrial fibrillation knowledge (JAFKQ), satisfaction with clinical care (7-point Likert scale) and motivation to maintain adherence to anticoagulation therapy (7-point Likert scale). Medication adherence will be measured at 90 day follow up (see table 1).

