### **7. Statistical considerations and Analysis:**

Analysis will follow intention to treat principles with all participants analysed in the arm they have been randomised to. P-values of  $< 0.05$  will be considered significant. Primary outcome analysis will use a two-tailed t-test to assess the difference between mean participant JAFKQ scores (max score = 100). Analysis will also be performed utilizing an Analysis of Covariance (ANCOVA), with baseline JAFKQ scores and education level incorporated into the model as covariates. A sample size of 200 participants (100 per arm) would, allowing for 15% attrition and assuming a standard deviation of 18 as described in other studies, have 90% power (2 sided, type 1 error of 5%) to detect an difference in 90-day AF knowledge of 8.95% between participants in the intervention and control arms of the study, which we consider a significant improvement in knowledge. Previous assessment of the JAFKQ has indicated participant scores 1 month post-test with no educational intervention are unchanged (60.4 [SD = 18.6] vs 62.3 [SD = 18.5];  $p = 0.551$ ).

For secondary analysis of satisfaction with clinical care, patient responses will be dichotomised into ‘satisfied’ ( $\geq 5/7$ ) vs ‘unsatisfied’ ( $\leq 3/7$ ). For medication adherence, patients will be classified as “adherent” or “not adherent as per page 11-12. Proportions in intervention vs control arms will be compared using a chi-squared test. Relative risk will be calculated using a log binomial unadjusted and adjusted for total time in clinic (for outpatients) and number of medications. Allowing for 15% attrition and assuming 60% satisfaction/medium or greater adherence in the control groups, a sample size of 200 (100 per arm) would have 90% power to detect a relative risk difference in satisfaction and adherence between control and intervention groups of 1.37 (that is, an increase from 60.0% to 82.2%).

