#### 1.6 Power and sample size

A sample size of 200 participants (100 per arm) would, allowing for 15% attrition and assuming a standard deviation of 18 as described in other studies, have 90% power (2 sided, type 1 error of 5%) to detect an difference in 90-day AF knowledge of 8.95% between participants in the intervention and control arms of the study, which we consider a significant improvement in knowledge. Previous assessment of the JAFKQ has indicated participant scores 1-month post-test with no educational intervention are unchanged (60.4 [SD = 18.6] vs 62.3 [SD = 18.5];  $p = 0.551$ ). Analysis will follow intention to treat principles with all participants analysed in the arm they have been randomised to. P-values of  $< 0.05$  will be considered significant. Primary outcome analysis will use a two-tailed t-test to assess the difference between mean participant JAFKQ scores (max score = 100%). Analysis will also be performed utilizing an Analysis of Covariance (ANCOVA), with baseline JAFKQ scores and education level incorporated into the model as covariates.

For secondary analysis of satisfaction with clinical care, patient responses will be dichotomised into ‘highly satisfied’ ( $\geq 6/7$ ) vs ‘not highly satisfied’ ( $\leq 5/7$ ). For medication adherence, patients will be classified as “adherent” or “not adherent”. Proportions in intervention vs control arms will be compared using a chi-squared test. Relative risk will be calculated using a log binomial unadjusted and adjusted for total time in clinic (for outpatients) and number of medications. Allowing for 15% attrition and assuming 60% satisfaction/medium or greater adherence in the control groups, a sample size of 200 (100 per arm) would have 90% power to detect a relative risk difference in satisfaction and adherence between control and intervention groups of 1.37 (that is, an increase from 60.0% to 82.2%).

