#### **Secondary outcome analysis:**

The significance of any difference between proportional secondary outcomes (satisfaction with clinical care, motivation to maintain adherence, actual medication adherence) will be analysed using a log binomial model adjusting for age (continuous), gender (male vs female), education (year 11 and above vs less than year 11), subtype of AF (categorical). A relative risk, 95% confidence interval and p-value will also be reported. Where baseline results are available, the corresponding baseline value results (e.g. discrete total score) will also be included as a covariate. Where this does not converge, a robust poisson will be fitted.

An unadjusted chi squared test will also be calculated with a corresponding relative risk, 95% confidence interval and p-value.

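### The SAP tests the 7-point satisfaction and motivation items only as the proportion scoring 6 or more; an ordinal test of the full score would use more of the data if the effect is a general shift

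*Combined protocol and SAP*

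**What the plan says.** Both documents schedule satisfaction once (after clinic or within 2 days) and motivation at baseline, at that same point and at 90 days, each on a 7-point Likert item.

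- **SAP 5.1** defines the outcomes by a cut at 6: "Satisfaction with clinic experience will be determined by a score of" at least 6, and "Motivation to maintain medication adherence will be determined by a score of" at least 6. It then states: "The proportion of participants achieving this outcome will be compared between intervention and control groups". SAP 1.2 and the footnote to eTable 9 use the same cut.
- **SAP 3.1** sets the test: "The significance of any difference between proportional secondary outcomes" is judged by a log binomial model adjusted for age, gender, education and AF subtype, plus the baseline value where one exists. Robust Poisson is the fallback, and an unadjusted chi-squared test is added. SAP 5.1.1 repeats this. Neither section plans an ordinal, rank or mean-score analysis.
- **Protocol section 7** gives another rule for satisfaction: "patient responses will be dichotomised into ‘satisfied" (5 or more) versus unsatisfied (3 or less). SAP 1.6 has "patient responses will be dichotomised into ‘highly satisfied" (6 or more) versus not highly satisfied (5 or less).
- **Protocol section 6** lists "motivation to maintain adherence to anticoagulation therapy (7-point Likert scale") without a cut-point.
- **Protocol section 7 and SAP 1.6** both assume 60% satisfaction in controls, 15% attrition and 90% power for 60.0% to 82.2%.

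**The concern.** Cutting an ordered scale in two treats a 1 and a 5 as the same answer, and a 6 and a 7 as the same answer. If the videos move people up generally, those movements are ignored. Three rows of eTable 9 are affected: satisfaction, motivation at 2 days and motivation at 90 days. The SAP calls these key secondary outcomes, and its secondary objectives ask whether patients are more satisfied and more motivated, which the full score addresses directly.

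For satisfaction there is a second problem. The result depends on a cut that the protocol and the SAP place differently, while the control rate behind the power statement stays the same.

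**Working it through.** **Inputs from the documents.** 100 per arm with 15% attrition gives 85 per arm. Two-sided 5%. Control rate 60%, target 82.2%.

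**1. The plan's own figure.** For two proportions with pooled null variance, power = Φ{[d√n − 1.96√(2p̄(1−p̄))] / √(p₁(1−p₁)+p₂(1−p₂))}.

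- 60% to 82.2%: d = 0.222, p̄ = 0.711. (0.222×9.220 − 1.96×0.641)/0.622 = 1.27, so power is 89.8%. The stated 90% reproduces.
- 60% to 75%: d = 0.15, p̄ = 0.675. (0.15×9.220 − 1.96×0.662)/0.654 = 0.13, so power is 55%.

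**2. Assumptions for the ordinal comparison.** The documents give no score distribution, so I took six 7-level control shapes, each with 60% at 6 or 7, and one common odds ratio across all cuts. The odds ratio is (0.75/0.25)/(0.60/0.40) = 2.0 for 60% to 75%, and (0.822/0.178)/(0.60/0.40) = 3.08 for 60% to 82.2%.

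**3. Formulas.** The information kept by the cut, relative to the seven levels, is 3p(1−p)/(1−Σp_k³), where p is the proportion at 6 or more. Ordinal power (Whitehead) is Φ{√[n(1−Σp̄_k³)/6]·ln OR − 1.96}, with p̄_k the average of the two arms.

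| Control % at scores 1 to 7 | Loss, control distribution | Loss, pooled (OR 3.08) | Ordinal power, 60→75% | Ordinal power, 60→82.2% |
|---|---|---|---|---|
| 3/4/6/10/17/30/30 | 23.4% | 31.1% | 70.4% | 97.9% |
| 3/4/6/10/17/20/40 | 21.9% | 26.4% | 68.5% | 97.2% |
| 2/3/5/10/20/15/45 | 19.7% | 22.6% | 66.6% | 96.5% |
| 8/8/8/8/8/10/50 | 17.4% | 18.0% | 64.5% | 95.6% |
| 8/8/8/8/8/30/30 | 23.7% | 31.2% | 70.5% | 98.0% |
| 0/0/2/5/33/10/50 | 14.1% | 16.5% | 63.5% | 95.3% |

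First row in full:

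- Loss at the control distribution: 3×0.6×0.4 = 0.72 and Σp³ = 0.0602, so 0.72/0.9398 = 0.766, a loss of 23.4%.
- Power for 60% to 75%: pooled Σp̄³ = 0.0844, so √(85×0.9156/6)×0.693 − 1.96 = 0.54, giving 70.4%.
- Power for 60% to 82.2%: pooled Σp̄³ = 0.1058, so √(85×0.8942/6)×1.1245 − 1.96 = 2.04, giving 97.9%.

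A simulation of chi-squared against Wilcoxon on five assumed shapes agrees: 54–55% versus 64–70% at odds ratio 2.0, and 90–91% versus 96–98% at 3.08.

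**4. Dependence on the satisfaction rule.** With the same shapes and odds ratio 3.08, at 85 per arm before any exclusion of 4s:

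| Rule | Relative risk | Power |
|---|---|---|
| 6 or more versus 5 or less (SAP) | 1.37 | 90% |
| 5 or more versus 4 or less | 1.05–1.28 | 29–84% |
| 5 or more versus 3 or less, 4s dropped (protocol) | 1.01–1.22 | 12–78% |

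**5. One 60% for two rules.** Let a and b be the control proportions scoring 4 and 5, with 60% at 6 or more. The protocol rule with 4s dropped then gives (0.60+b)/(1−a). Setting this to 0.60 requires b = −0.6a, so a = b = 0. The two rules share a 60% rate only if nobody scores 4 or 5.

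**The case against.** **The gain depends on how the effect acts.** This is the strongest point against, and it stands. Take a control distribution of 2/3/5/10/20/35/25% and an effect that only moves people into category 6, drawn proportionally from the lower scores. The binary test then has 54% power against 27% for Wilcoxon at 60% to 75%, and 90% against 51% at 60% to 82.2%. The ordering reverses, and the documents do not say which pattern to expect.

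**The high-score proportion is the chosen outcome, and a relative risk is easier to read.** This stands as a reason to keep the relative risk. It is not a reason to have no full-scale analysis.

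**The larger gain uses an effect the plan does not name.** True: 60% to 75% is this review's choice. At the plan's own effect the gain is from 90% to about 96–98%.

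Four stronger readings might be inferred, and the documents do not support them:

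- *The cut-point conflicts for both scales.* The protocol sets no motivation cut-point, so only satisfaction is in conflict.
- *The SAP cut drops respondents or leaves room for a later choice.* Its two classes cover every score, and SAP 1.2, 1.6, 5.1 and eTable 9 agree on 6. Only the protocol rule leaves a score of 4 unplaced.
- *About 30% of the information is lost as a matter of fact.* That is the upper part of an assumption-based range.
- *The sample-size statement is wrong.* It reproduces for the binary outcome.

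**Conclusion.** The point holds as a low-severity improvement to secondary outcomes; the primary knowledge score is already analysed on its full scale. The estimated loss of roughly 15–30% is conditional on a general shift across the scale and on assumed shapes with 60% of controls at 6 or more. It would be larger with a ceiling: about 47–67% if 82–90% of respondents score 6 or more. Carrying the 60% rate over to motivation is a further assumption, because the plan states it only for satisfaction and adherence.

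The mismatch in the satisfaction rule needs no such assumptions. It is visible in the text, and the shared 60% cannot describe both rules unless nobody scores 4 or 5.

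**What to change.** 1. In SAP 3.1, 5.1 and 5.1.1, make a proportional-odds model on the full 7-point score the test for satisfaction and for motivation at 2 and 90 days. Use the covariates already listed in SAP 3.1, and baseline motivation for the motivation outcomes (satisfaction has no baseline measure).
2. In eTable 9, report the common odds ratio with its 95% CI and p-value. Beside it keep the proportion scoring 6 or more with its adjusted relative risk and 95% CI.
3. Reconcile the satisfaction rule between protocol section 7 and SAP 1.6, including where a score of 4 goes, and tie the 60% control rate to the rule retained. State that the motivation cut is introduced in the SAP.

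The cost is SAP wording and one standard model, with no new data or patients. The downside is that a common odds ratio is harder to explain than a relative risk, and power can fall if the effect lies only across the cut at 6. The retained relative risk makes that pattern visible.

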#### 5.1.1 Satisfaction with clinic, motivation to maintain medication adherence and medication adherence – Analysis

Key secondary outcomes (satisfaction, motivation to maintain medication adherence and medication adherence) will be assessed utilising a log binomial adjusting for age, gender, educational level and sub-type of AF. This analysis is encompassed within table 9.

An unadjusted chi-squared test will also be performed comparing these two outcomes.

#### 5.1.2 As treated analysis of primary and secondary outcomes:

An as treated analysis of all primary and secondary outcomes will also be performed to assess the impact of intervention engagement on study outcomes.

Highly engaged participants will be defined as those watching the video series 3 or more times throughout the intervention period. Moderately engaged participants those watching the series 1-2 times, and poorly engaged participants those who did not watch the video series. Each intervention group will be compared to the control group in the same analyses described above (tables 10-12).

*eTable 10: Sub-group analysis of poorly engaged intervention participants*

|  | Control | Poorly | RR [95% CI] | RR [95% CI] | p-value |
|--|---------|--------|-------------|-------------|---------|
|--|---------|--------|-------------|-------------|---------|

|                                                                    | N C (%)                  | engaged
Intervention
N T (%) | (Control vs
CPR video)
[unadjusted] | (Control vs
CPR video)      | [adjusted] |
|--------------------------------------------------------------------|-------------------------------------|-----------------------------------------------|-------------------------------------------|--------------------------------|------------|
| Jessa Atrial Fibrillation Knowledge Questionnaire score (%) |                                     |                                               |                                           |                                |            |
| Mean score 2
days post
intervention                          | (n=xx)
Mean (SD)
Median (IQR) | (n=xx)
Mean (SD)
Median (IQR)           |                                           | Mean
Difference
(95% CI) | p-value    |
| Mean score 90
days post
intervention                         | (n=xx)
Mean (SD)
Median (IQR) | (n=xx)
Mean (SD)
Median (IQR)           |                                           | Mean
Difference
(95% CI) | p-value    |
| Satisfaction                                                |                                     |                                               |                                           |                                |            |
| Highly
satisfied*                                               | (n=xx)
Proportion
(%)         | (n=xx)
Proportion (%)                      |                                           | RR (95% CI)                    | p-value    |
| Motivation to maintain medication adherence                 |                                     |                                               |                                           |                                |            |
| Highly
motivated* 2
days post
intervention                | (n=xx)
Proportion
(%)         | (n=xx)
Proportion (%)                      |                                           | RR (95% CI)                    | p-value    |
| Highly
motivated* 90
days post
intervention               | (n=xx)
Proportion
(%)         | (n=xx)
Proportion (%)                      |                                           | RR (95% CI)                    | p-value    |
| Medication adherence                                        |                                     |                                               |                                           |                                |            |
| Adherent** to
medications 90
days post
intervention       | (n=xx)
Proportion
(%)         | (n=xx)
Proportion (%)                      |                                           | RR (95%
CI)                 | p-value    |

*eTable 11: Sub-group analysis of moderately engaged intervention participants*

|                                                                    | Control
N C (%)       | Moderately
engaged
Intervention
N T (%) | RR [95% CI] (Control vs
CPR video) | p-value |
|--------------------------------------------------------------------|-------------------------------------|-------------------------------------------------------------|---------------------------------------|---------|
| Jessa Atrial Fibrillation Knowledge Questionnaire score (%) |                                     |                                                             |                                       |         |
| Mean score 2 days post
intervention                             | (n=xx)
Mean (SD)
Median (IQR) | (n=xx)
Mean (SD)
Median (IQR)                         | Mean Difference (95% CI)              | p-value |
| Mean score 90 days post
intervention                            | (n=xx)
Mean (SD)
Median (IQR) | (n=xx)
Mean (SD)
Median (IQR)                         | Mean Difference (95% CI)              | p-value |
| Satisfaction                                                |                                     |                                                             |                                       |         |
| Highly satisfied*                                                  | (n=xx)
Proportion (%)            | (n=xx)
Proportion (%)                                    | RR (95% CI)                           | p-value |
| Motivation to maintain medication adherence                 |                                     |                                                             |                                       |         |
| Highly motivated* 2
days post intervention                      | (n=xx)
Proportion (%)            | (n=xx)
Proportion (%)                                    | RR (95% CI)                           | p-value |
| Highly motivated* 90
days post intervention                     | (n=xx)
Proportion (%)            | (n=xx)
Proportion (%)                                    | RR (95% CI)                           | p-value |
| Medication adherence                                        |                                     |                                                             |                                       |         |
| Adherent** to
medications 90 days post
intervention          | (n=xx)
Proportion (%)            | (n=xx)
Proportion (%)                                    | RR (95% CI)                           | p-value |

*eTable 12: Sub-group analysis of highly engaged intervention participants*

|                                                                    | Control
NC (%) | Highly engaged
Intervention
NT(%) | RR [95% CI] (Control vs
CPR video) | p-value |
|--------------------------------------------------------------------|--------------------------------------|-------------------------------------------------------------|-----------------------------------------------|----------------|
| Jessa Atrial Fibrillation Knowledge Questionnaire score (%) |                                      |                                                             |                                               |                |
| Mean score 2 days post
intervention                             | (n=xx)
Mean (SD)
Median (IQR)  | (n=xx)
Mean (SD)
Median (IQR)                         | Mean Difference (95% CI)                      | p-value        |
| Mean score 90 days post
intervention                            | (n=xx)
Mean (SD)
Median (IQR)  | (n=xx)
Mean (SD)
Median (IQR)                         | Mean Difference (95% CI)                      | p-value        |
| Satisfaction                                                |                                      |                                                             |                                               |                |
| Highly satisfied*                                                  | (n=xx)
Proportion (%)             | (n=xx)
Proportion (%)                                    | RR (95% CI)                                   | p-value        |
| Motivation to maintain medication adherence                 |                                      |                                                             |                                               |                |
| Highly motivated* 2
days post intervention                      | (n=xx)
Proportion (%)             | (n=xx)
Proportion (%)                                    | RR (95% CI)                                   | p-value        |
| Highly motivated* 90
days post intervention                     | (n=xx)
Proportion (%)             | (n=xx)
Proportion (%)                                    | RR (95% CI)                                   | p-value        |
| Medication adherence                                        |                                      |                                                             |                                               |                |
| Adherent** to
medications 90 days post
intervention          | (n=xx)
Proportion (%)             | (n=xx)
Proportion (%)                                    | RR (95% CI)                                   | p-value        |

